### Economic evaluation

An economic evaluation will be performed to investigate the cost-effectiveness of the intervention compared to usual care. Cost-effectiveness will be expressed in terms of the cost per quality adjusted life year (QALY) gained and via the net monetary benefit approach. Healthcare costs will be assessed via the iMCQ. Lost productivity costs will not be evaluated, as all participants are retired at an age of 70 years or older. Standard cost-prices per item of healthcare consumption will be determined via appendix 1 of the guideline for performing economic evaluations [43]. If standard prices are not available, the full cost prices of items will be used via activity-based costing. The costs of medication use will be derived from the Dutch formulary [44], increased with the cost for pharmacy care and will be based on the medication use confirmed during the follow-up telephone calls or the medication list from the community pharmacy. The costs of the intervention will be calculated through a time measurement of the intervention, which is based on the time spent by the pharmacotherapy-team members on the TMPC elements, and their average salary. For all participants, an overall time estimate will be made and in a selected group an exact time measurement per TMPC element will be executed. QoL will be measured by the EQ-5D-5L, which includes the Visual Analogue Scale. Furthermore, a budget impact analysis will be performed. The short- and midterm affordability of TMPC will be assessed from governmental, health care and insurer perspectives.

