### Intervention

A pharmacotherapy-team conducts the intervention during the initial hospital stay (i.e. the index hospitalization). This pharmacotherapy-team involves collaboration between physicians and pharmacists, and this multidisciplinary team aims to exchange knowledge. The team is composed of senior staff members with at least one medical specialist and one hospital pharmacist, both of whom are preferably registered as clinical pharmacologists. Other potential team members may include residents in internal medicine or geriatrics, clinical pharmacology trainees or hospital pharmacy residents, who participate with the supervision of a senior staff member. All pharmacotherapy-team members conducting the TMPC are trained in the standardized intervention prior to study initiation during a live training session. This session is recorded to be viewed by new pharmacotherapy-team members as e-learning.

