The TMPC intervention is based on the Systematic Tool to Reduce Inappropriate Prescribing (STRIP) methodology [26], which is a structured method for medication reviews developed to improve appropriate prescribing. Prior to the start of the intervention, a medication reconciliation must be performed to ensure that the medication lists are as accurate as possible [27]. Medication reconciliation is a standardized process during hospitalization in the Netherlands, and therefore part of the usual care in all hospitals participating in this trial. The TMPC comprises four elements of which the sequence can be adjusted to meet the needs of the pharmacotherapy-team and patient:A structured pharmacotherapeutic analysis is performed by the pharmacotherapy-team, who identifies pharmacotherapeutic problems such as over- and undertreatment, ineffective treatment, side effects, clinically relevant contraindications and interactions, appropriateness of dosing, and usage problems. Several tools can be used to aid the pharmacotherapeutic analysis, such as the Dutch translation of the STOPP-START criteria [28], and the local clinical decision support system alerts from the hospital information system. Additionally, the tools mentioned in the Dutch national multidisciplinary guideline on 'Polypharmacy in older people' with the module 'Reducing and stopping medication’ (2020) [28, 29], such as the factsheets on deprescribing [30], can be applied during pharmacotherapeutic analysis. The collection of clinical and laboratory data from electronic health records (EHRs) is necessary for optimizing the individual patients’ pharmacotherapy. The GP, elderly care physician (also known as the nursing home physician) and/or community pharmacist are consulted if essential information in the medical or medication record is missing or unclear. Usually, Dutch patients are registered at one GP-practice and one community pharmacy.A transitional multidisciplinary discussion is organized together with the responsible physician in the hospital (medical specialist, medical resident/intern) and one or more members of the pharmacotherapy-team. If a proposed change involves prescriptions from another medical specialist, it is discussed with that specialist. The GP or elderly care physician is consulted to discuss the results of this pharmacotherapeutic analysis and to make arrangements about the follow-up of recommendations after hospital discharge. If community pharmacists should be actively involved in the follow-up/monitoring process of interventions, they will be contacted by the pharmacotherapy-team if deemed necessary.An interview and discussion with the patient and/or legal representative are conducted before discharge by a member of the pharmacotherapy-team. The recommendations described in the pharmacotherapeutic plan are discussed and adjusted, utilizing shared decision-making techniques [31]. Motivational interviewing is used to address problems and needs within the medication plan. To assess the understanding of the patient and/or legal representative the teach-back method is used [32]. If needed, instructions on medication use are explained and adjustments can be made in the pharmacotherapeutic plan by the pharmacotherapy-team after discussion with the patient and/or legal representative.A discharge letter with a detailed pharmacotherapeutic plan is drafted by a member of the pharmacotherapy-team. This letter includes identified DRPs and associated changes made during hospitalization and/or advice on pharmacotherapy (such as initiating, discontinuing, or tapering) after hospital discharge in comparison with the medication used at the moment of admission. Additionally, the rationale for these recommendations and arrangements made for follow-up and monitoring are described. The letter is standardized and has a similar layout in all hospitals, it is addressed to the GP or elderly care physician (it can be found in Supplementary Material 1 ). It can be a separate letter or incorporated into the discharge letter of the admitting specialist. A copy is provided to the patient, community pharmacist and all relevant healthcare professionals involved in the patient’s treatment.

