### Data collection

Baseline data collection is conducted by the local research team during index hospitalization. All local research personnel are trained in data collection through e-learning. At baseline, information is collected about demographics, independence of medication intake, use of medication aids, living situation, falls and fall-related injuries, laboratory results (e.g., electrolytes, renal function; collected in routine care), medical history, reasons for current admission and medication use at both admission and discharge. Furthermore, we collect data through various questionnaires, including EuroQol 5-dimensions 5-level (EQ-5D-5L) [33] for quality of life (QoL), the Katz-6 [34] for activities of daily living (ADL), the Clinical Frailty Scale [35] for frailty, and the iMTA medical consumption questionnaire (iMCQ) [36] for healthcare utilization and costs. In addition, data collection in intervention hospitals includes information about the recommendations given during the pharmacotherapeutic analysis, completeness of conducting TMPC elements and healthcare professionals involved, and duration of TMPC.

Outcome data are collected by a central research team during follow-up telephone calls with participants or their representatives at three time points: 30 days, 3 months and 12 months after discharge from the index hospitalization. Data concerning current living situation, falls and fall-related injuries, independence of medication intake, use of medication aids and current medication use are collected. Furthermore, the EQ-5D-5L, Katz-6 ADL and iMCQ questionnaires are repeated during each telephone interview. All central research employees are trained in performing the follow-up data collection. If a patient or representative cannot be reached after four attempts or if a patient does not wish to answer the questionnaires anymore but still wants to continue study participation, the patient’s GP or elderly care physician is contacted to ask only those questions required to answer the primary research objective.

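### TMPC is costed from pharmacotherapy-team time and salary alone, although the intervention also uses the time of the responsible hospital physician and the GP

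*Protocol article*

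**What the plan says.** Protocol article, Economic evaluation: the cost of TMPC comes from a time measurement that is "based on the time spent by the pharmacotherapy-team members on the TMPC elements, and their average salary". An overall time estimate is made for all participants, and exact timing per element in a selected group. Other healthcare use comes from the iMCQ at standard prices; where none exists, "the full cost prices of items will be used via activity-based costing". Medication is valued from the national formulary plus pharmacy-care cost. The results feed cost per QALY, net monetary benefit and a budget impact analysis from governmental, health care and insurer perspectives.

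Intervention section, on who is in the team: "The team is composed of senior staff members with at least one medical specialist and one hospital pharmacist". Supervised residents and trainees may join. The GP, the community pharmacist and the physician treating the patient on the ward are not listed.

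Intervention section, on who takes part in the transitional multidisciplinary discussion:
- The discussion is held "together with the responsible physician in the hospital (medical specialist, medical resident/intern) and one or more members of the pharmacotherapy-team".
- "The GP or elderly care physician is consulted to discuss the results of this pharmacotherapeutic analysis", and follow-up after discharge is arranged in the same contact.
- "If a proposed change involves prescriptions from another medical specialist, it is discussed with that specialist".
- Community pharmacists with an active part in follow-up are involved conditionally: "they will be contacted by the pharmacotherapy-team if deemed necessary".

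Data collection section: intervention hospitals record "completeness of conducting TMPC elements and healthcare professionals involved, and duration of TMPC".

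**The concern.** The costing rule and the description of the intervention do not cover the same people. Contact between the hospital team, the treating physician and primary care is what makes TMPC transitional and multidisciplinary, yet the rule prices only one side of each conversation. The other source of care costs is the iMCQ, answered by patients or their representatives by telephone. Nothing in the article says that it records consultations between professionals.

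There is also a difference in valuation. Care items get a standard or full cost price, while the team's own time is valued at average salary. The article does not define that term, so it is unclear whether employer and overhead costs are included.

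Cost-effectiveness is a named secondary outcome, and the Discussion relies on it to weigh the effort of TMPC against its benefit. A TMPC cost that leaves out known inputs weakens that comparison. The budget impact analysis is exposed most directly, because its health care perspective reaches beyond the hospital team into primary care.

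**Working it through.** The article states no cost, time or wage for TMPC, so there is no figure to reproduce. The check has three parts.

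**1. Inputs used against inputs costed**

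| Professional | Part in TMPC (Intervention section) | In the costing rule? |
|---|---|---|
| Pharmacotherapy team | All elements | Yes, at average salary |
| Responsible hospital physician | Discussion, unconditional | No |
| GP or elderly care physician | Discussion, unconditional | No |
| Other specialist | Only if their prescription is affected | No |
| Community pharmacist | Only if judged necessary | No |

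The Discussion describes a telephone call to both GP and community pharmacist as a general feature. The Methods make the pharmacist's contact conditional, so I treat only the two unconditional rows as firm.

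**2. Direction**

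Let x be the mean cost per intervention patient of non-team time. Write ΔC and ΔE for incremental cost and QALYs, and λ for the value placed on a QALY.
- If x is left out, the reported incremental cost is ΔC − x.
- Net monetary benefit is λΔE − ΔC, so the reported value is too high by exactly x per patient.
- Cost per QALY is ΔC/ΔE, so for ΔE > 0 the reported value is too low by x/ΔE.
- Let r_C and r_I be the mean cost per patient of uncosted usual-care review work in the control and intervention arms. The net understatement of ΔC is then x − (r_C − r_I). The offset matters only so far as control patients receive more such work than intervention patients.

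**3. Illustrative size (assumed inputs)**

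Assume 10 to 60 minutes of non-team time per patient at 40 to 120 euro per hour, and x = minutes/60 × hourly cost. The Sample size calculation section plans 2,576 inclusions, so 2,576/2 = 1,288 per arm.
- Low: 10/60 × 40 = 6.7 euro per patient; over 1,288 patients, about 8,600 euro.
- Middle: 30/60 × 80 = 40 euro per patient; over 1,288 patients, 51,520 euro.
- High: 60/60 × 120 = 120 euro per patient; over 1,288 patients, about 154,600 euro.

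If the team itself spends an assumed 60 to 180 minutes, the omitted share of total TMPC time runs from 10/(10 + 180) = 5% to 60/(60 + 60) = 50%. A range this wide shows that the documents do not fix the size.

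These figures cover non-team time only. Any gap between average salary and full hourly cost for the team would come on top and cannot be estimated from the article.

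**The case against.** The strongest reply is that cost-effectiveness depends on the difference between arms. The Comparator section allows a medication review by the prescribing physician or consulting pharmacist, provided it does not involve all TMPC elements, and no separate time costing is stated for it. The article also says that some TMPC elements already occur in standard practice. This stands: the net direction of the bias in incremental cost is not proven, and only the direction of the TMPC component is. It does not justify leaving out known TMPC inputs, because nothing shows that the two omissions cancel.

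A second reply is that this is a condensed article and a health-economic plan may fill the gap. That would answer silence. Here the article states a rule that names whose time is counted, and the rule conflicts with its own account of who delivers TMPC. By contrast, the article says nothing either way about the cost of training the teams, which may well be left to the fuller plan, so it is not part of this point.

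A reader might go further and infer that intervention cost is understated by roughly a third to a half. That needs assumed team minutes, assumed non-team minutes and an assumed mark-up on salary, none of which the article gives. It would also be a share of TMPC cost alone, not of incremental cost. Nor can one say that everything except TMPC is valued at standard or full cost price, since medication is valued from the formulary.

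**Conclusion.** The point holds as to the TMPC cost component. Followed as written, the rule omits the time of the responsible hospital physician and the GP or elderly care physician, and in some patients that of another specialist or the community pharmacist. The component is therefore too low and, other things equal, all three economic results lean towards TMPC.

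The size is unknown. The 7 to 120 euro per patient rests wholly on the assumed minutes and hourly costs. It may be small beside readmission costs, and usual-care reviews may offset part of it. The documents do not support the inference that a cost-effectiveness conclusion would be reversed. They also do not settle whether the iMCQ could pick up any of this time; they only give no sign that it does. The matter concerns one component of a secondary outcome and is worth correcting because the correction is cheap.

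**What to change.** Amend the costing rule in the health-economic plan:
- Cost every professional recorded as involved in a TMPC element, not only team members, at the guideline's standard price or, where none exists, full cost per hour.
- Where non-team minutes were not measured, assign assumed minutes with a stated low-to-high range and carry that range through cost per QALY, net monetary benefit and budget impact. The element-level timings in the selected group are a starting point, since each party to a conversation spends about the same time in it.
- Value team time on the same full-cost basis, and say what the hourly figure includes.
- Report the team-salary-only figure as a sensitivity analysis.
- State as a limitation that usual-care reviews are not separately time-costed.

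Trial status says that inclusion ended in January 2025, and TMPC is delivered around the index stay, so prospective timing of non-team staff is no longer realistic. The fix therefore relies on the involvement and duration data already collected. The cost is a little more analysis work and a somewhat less favourable intervention cost; trial conduct does not change.

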### Comparator – usual care

The comparator in this study is usual care, which refers to the entire spectrum of drug-related interventions by various healthcare providers (i.e. physicians, pharmacists, nurses) during hospital admission. This may include a medication review being performed by the prescribing physician or consulting pharmacist in accordance with usual care, which is allowed if it does not involve all the elements of TMPC.

Because usual care may differ across hospitals, the usual pharmacotherapeutic care in all participating hospitals was explored via a detailed questionnaire prior to the start of the study. A translated version of the questionnaire is available upon request.

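### TMPC staff time is priced at average salary while other care is priced at standard or full cost, so on a literal reading the unit price of TMPC labour is too low

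*Protocol article*

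**What the plan says.** All the costing rules are in the protocol article, Methods, Economic evaluation.

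- Care with a reference price: "Standard cost-prices per item of healthcare consumption will be determined via appendix 1 of the guideline for performing economic evaluations".
- Care without one: "If standard prices are not available, the full cost prices of items will be used via activity-based costing".
- Medication: formulary prices, with a stated addition for pharmacy services.
- The intervention: a time measurement combined with pay, that is, "time spent by the pharmacotherapy-team members on the TMPC elements, and their average salary". The section does not say whether the salary figure includes employer charges, paid non-productive hours or overhead.

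The results enter two measures: "Cost-effectiveness will be expressed in terms of the cost per quality adjusted life year (QALY) gained and via the net monetary benefit approach". A budget impact analysis is also planned: "The short- and midterm affordability of TMPC will be assessed from governmental, health care and insurer perspectives". No unit prices are stated for it.

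The Intervention section describes who supplies the time: "The team is composed of senior staff members with at least one medical specialist and one hospital pharmacist". It adds that residents and trainees may take part under supervision.

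**The concern.** An economic comparison should value resources on one basis. Here the care that TMPC might avoid, such as a readmission, is valued at standard or full cost. The labour used to avoid it is valued, as worded, at pay alone. Pay is normally less than the cost of an hour of work to the hospital, because it leaves out employer charges, overhead and paid hours that are not productive.

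TMPC staff time is the cost that the intervention adds by design. The Discussion calls the intervention time-consuming and relies on the cost-effectiveness analysis to weigh effort against benefit. A low hourly price passes directly into the incremental cost, and from there into cost per QALY and net monetary benefit. On its own it makes both look better for TMPC than a consistent price basis would.

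The point concerns the price per hour only. Whose hours are counted is a separate question.

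**Working it through.** The document states no cost figure for TMPC, so there is nothing to reproduce. What can be checked is how the stated rule behaves.

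**Inputs**
- Price rule for TMPC (team time and average salary) and price rule for other care (standard or full cost): Economic evaluation section.
- H, team hours per patient; S, hourly salary; k, full hourly cost divided by hourly salary: none is in the document. All values below are assumptions.

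**Step 1: relative size.** Planned TMPC staff cost = H × S. Full cost = k × H × S. Understated share = 1 − (H × S)/(k × H × S) = 1 − 1/k.

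| k (assumed) | 1 − 1/k |
|---|---|
| 1.0 | 0% |
| 1.3 | 23% |
| 1.5 | 33% |
| 2.0 | 50% |

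H and S cancel, so the share depends on k alone.

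**Step 2: absolute size.** Amount missing per patient = (k − 1) × H × S. With 1 to 4 team hours at EUR 40 to 80 per hour (both assumed):
- k = 1.2: 0.2 × 1 × 40 = EUR 8, up to 0.2 × 4 × 80 = EUR 64.
- k = 1.5: 0.5 × 1 × 40 = EUR 20, up to 0.5 × 4 × 80 = EUR 160.
- k = 2.0: 1.0 × 1 × 40 = EUR 40, up to 1.0 × 4 × 80 = EUR 320.

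**Step 3: effect on the planned measures.** Net monetary benefit is the willingness to pay times the QALY gain, minus the incremental cost. It rises by (k − 1) × H × S per patient, whatever the willingness to pay. Cost per QALY falls by (k − 1) × H × S divided by the QALY gain, if that gain is positive. The document gives no expected QALY gain, no threshold and no readmission cost. It therefore cannot be said whether either shift could change a conclusion.

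**Step 4: does usual care cancel it?** The Comparator section allows reviews in control hospitals: "This may include a medication review being performed by the prescribing physician or consulting pharmacist in accordance with usual care". No costing of that staff time is stated. Suppose TMPC replaces review work equal to a share u of TMPC time. The true increment, relative to the planned H × S, is then k × (1 − u). At k = 1.35 (assumed):
- u = 0: 1.35
- u = 0.25: 1.35 × 0.75 = 1.01
- u = 0.5: 1.35 × 0.5 = 0.68

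The total incremental cost could therefore be too low, about right or too high. This offset comes from hours left out, not from the price per hour. If C control hours per patient were also counted at salary, the increment would be S × (H − C), still short of k × S × (H − C) by the share 1 − 1/k whenever H exceeds C.

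**The case against.** The strongest objection is that average salary is not defined. In one clause of a condensed article it may stand for a staff cost rate that already includes employer charges and overhead. Then k = 1 and nothing is understated. Detailed rates would normally be in the full protocol or an economic analysis plan, which are not shown. This stands as a limit on certainty. The literal reading is still the more natural one: the same section says full cost where it means full cost, and states a mark-up where it intends one, for medication. If the salary figure is already loaded, the sentence should say so.

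The full-cost fallback is also worded for items of healthcare consumption, and the intervention has its own sentence. Timing each element and multiplying by a staff rate is itself an activity-based method. This stands too. A strict breach of the plan's own rule is not shown; what is shown is two price bases within one comparison.

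Uncosted usual-care reviews could offset the effect, as step 4 shows. In the other direction, the stated intervention costing names only team time, although "The GP or elderly care physician is consulted to discuss the results of this pharmacotherapeutic analysis". So the net error in the total incremental cost has no fixed sign. A reader might infer that the incremental cost must come out too low; the document does not support that.

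A reader might also infer that the budget impact analysis will use the salary price. No unit prices are given for it, so this would be a guess.

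**Conclusion.** The point holds as a defect in a stated costing rule. Followed as written, the rule understates the unit price of TMPC labour by 1 − 1/k and, taken alone, biases cost per QALY and net monetary benefit towards TMPC. The share runs from 0% at k = 1 to 50% at k = 2.0, and k is assumed throughout. The amount in euros cannot be computed from the document and may be small next to the cost of readmissions.

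It does not follow that the economic results will favour TMPC. A bias in one direction is not a result, and nothing in the document shows that this one could reverse a conclusion. Cost-effectiveness is a secondary outcome. The time data are unaffected, and so is the primary analysis of DRAs within 30 days.

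**What to change.** In the economic analysis plan, replace average salary by the full cost price per productive hour for each profession: salary plus employer charges plus overhead, divided by productive hours. If the intended salary figure already includes these, state that instead.

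Then:
- value any usual-care review time that is costed on the same basis;
- use the same hourly price in the budget impact analysis wherever full cost is the relevant price for the perspective taken;
- show a salary-only calculation as a sensitivity analysis at most.

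The cost is about one sentence and a change of hourly rates in the cost model. No new patient data are needed, because time is already being measured and the rate is applied at analysis. The downside is a somewhat higher stated cost of TMPC.
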